### **6.1 Overview of Participant Procedures**

#### Recruitment and Randomization

1. Potential participants will be identified by one of four recruitment methods previously described.
2. RAs will screen patients for eligibility and discuss the study protocol in detail. If the patient is deemed eligible to participate he/she will complete written informed consent and HIPAA authorization.

3. Enrolled participants will schedule an appointment at the UIC Clinical Interface Core (CIC) to complete baseline data collection, which includes a blood draw.
4. Participants randomized to *mDAS* will receive the intervention component in Year 1, while participants randomized to *Usual Care* will receive it in Year 2. RAs will inform participants of assignment.

#### **Additional information for mDAS Sleep Sub-study Supplement**

5. English-speaking participants will be asked to participate in a sleep sub-study to evaluate his or her sleep for 9 days at one of the regularly scheduled data collection follow up visits for the parent study.
6. RAs will screen willing participants for the sleep sub-study for eligibility and discuss the study protocol in detail. If the patient is interested, he/she will complete written informed consent for the sleep sub-study and complete the questionnaires. He/she will take an actiwatch to wear day and night for 7 days. Each day, they will receive mytapp messages asking about their sleep quality and process the night before. The Actiwatch will be returned at patient's convenience (drop it off or RA will pick it up). Reimbursement for the entire study is \$40.

#### Usual Care Component

1. Participants will receive contact information for a diabetes educator and a clinical pharmacist for medication reconciliation.
2. Patients will receive a one-page contact sheet with the names and phone numbers of their local healthcare team as well as paper-based, low-literacy diabetes educational information.

#### mDAS - Pharmacist Component

1. Pharmacists will provide medication and disease management services to patients by following a Pharmacist Management Protocol (see attached).
2. The initial pharmacist videoconference will include medication reconciliation and review therapeutic goals.
3. Follow up videoconferences will occur every other month. The interval duration may increase/decrease based on individual preference and when subjects reach goals.
4. These subsequent visits will involve an evaluation of adherence, medication reconciliation, and a review of home glucose and/or blood pressure monitoring data, an evaluation of drug interactions and side effects, goal setting, basic lifestyle

modifications, pillbox use, development of a low-literacy medication list, and other adherence aids.

5. Pharmacists will adjust therapy according to the plan of care under PCP guidance and notify PCPs of agreed upon modifications through EMR notifications. Side effects will be conveyed to the PCP (if the PCP is not available, the covering physician will be contacted as per Pharmacist management Protocol).
6. Pharmacists will forward all electronic progress notes to PCP EMR "Inbox" after each encounter.
7. If the PCP feels that the patient should not remain in the study the provider can inform the Co-PIs to disenroll the participant.

#### mDAS - Health Coach Component

1. All health coaches will receive standardized training/re-training via two educational curricula: (1) the *Diabetes Education Empowerment Program*; (2) [name] *Training Curriculum for Health Coaches*; and (3) PEARLS for problem solving in depression management.
2. The coaches will communicate with their patients through home visits, phone calls, clinic encounters, and text messaging. Coaches will use *mytapp* to schedule text messages (messages will be tailored to individual and reflect patient goals).
3. Coaches may evaluate food inventory, medication adherence, and insulin injection techniques. Coaches will check glucose levels and blood pressures as needed.
4. Coaches may show Living Well with Diabetes lessons via iPad for education.
5. Coaches will participate in goal setting procedures. They will use the Purple Binder to access community resources.
6. Coaches will facilitate videoconferencing with patients. A multidisciplinary meeting will include coaches and pharmacists to communicate on a weekly basis about active participant issues.
7. Coach activity will be collected on a standardized electronic form completed after every participant contact. Coaches will document contact in the EMR.

#### Crossover Transition

1. One year after enrollment, the participants receiving *mDAS* will have the intervention components phased out to assess maintenance. The participants in the usual care group during year 1 will receive *mDAS* support for the subsequent year to assess intensification.
2. Coaches will help participants enlist social support and community resources for long term assistance with medications.

3. Coaches may periodically be contacted by disengaged participants during the following year. These communications will be logged.

#### Retention

1. Monetary reimbursement for each data collection
2. Periodic phone calls to verify address and phone data
3. Use of secondary alternative contact information
4. Any “lost” individuals will be searched for using a comprehensive standardized web based search protocol which included:
  - a. Five people locators
  - b. Major social networking sites, specifically those with more minority involvement
  - c. Department of corrections database
  - d. These searches will be conducted on the target individual as well as secondary contacts
  - e. All potential contact will be private. No study related information will be conveyed in public through these searches.

#### Health Coach Fidelity

1. To continuously evaluate the fidelity of the pharmacist and health coach components of the intervention, investigators will review health coach and patient medical records of 10% of participants randomly selected.
2. In addition, we will monitor health coach activities through encounter forms that include participant interactions and duration of time spent on activities.
3. Drs. [name] and [name] will attend multidisciplinary weekly meetings with health coaches and pharmacists and review active patient issues.

#### Data Collection

1. This research will be performed at the CCTS Clinical Interface Core.
2. Surveys will be conducted by interview format. This information is only being collected for research and will not be shared with others. This will take approximately 60 minutes.
3. We will draw some blood from each subject’s arm to measure Hemoglobin A1c and cholesterol profile. Each subject will be asked to fast (may drink water but may not eat food for 12 hours prior to the test). The amount of blood drawn will be about 6 ml (approximately one teaspoon).

- a. Briefly, a total of 6 ml of whole blood will be collected in one gold SST top vacutainer tube and one lavender EDTA tube on each of the blood draws.
  - b. Once collected the blood will be delivered to the Alverno lab for processing.
4. Each subject's height, weight, and blood pressure will be measured, similar to how this is done in the doctor's office.
5. The subject will provide contact information for all of the pharmacies where prescriptions have been filled for the past year. The subject will allow study personnel to contact these pharmacies to collect information on the type, number, and dates of prescriptions filled.
6. Each subject will be asked to return after 6, 12, 18, and 24 months for similar testing (surveys, blood tests, height, weight, blood pressure).

#### **Additional Data Collection for mDAS Sub-study Supplement**

7. Each subject will be asked to complete surveys in interview format on personal sleep practices. The surveys include: Pittsburgh Sleep Quality Index, PROMIS Sleep-related Impairment Short Form 8a (8 items) and PROMIS Sleep Disturbance Short Form 8b (8 items), an assessment of sleep apnea and restless leg syndrome. This will take approximately 20 minutes. Patients will be compensated \$10 for this initial sleep sub-study data collection.
8. The RA will provide instructional tutorial on using the wrist actigraphy (Actiwatch) to the participants. This will take approximately 5 minutes
9. Study participants will wear a wrist actigraphy for 7 days and 7 nights and answer custom questions on sleep after the participants wake up. The participant has the option of answering the questions via myTapp messages or through a web-based online sleep diary survey using a secure application such as REDCap or Qualtrics. These questions will be modified from a validated consensus sleep diary.
10. At the end of the 9 days, participants will be telephoned to complete a post-study evaluation and to schedule a day/time to return the actigraph watch.
11. Participants will be compensated \$30 for sub-study completion by research personnel.

**On the consent form, participants will be asked for permission to use the data collected within the larger mDAS study as part of the analyses in this sub-study. Patients are allowed to decline and still participate in this portion of the research.**

#### **Temporary modifications to data collection during COVID-19 pandemic**

Due to the COVID-19 pandemic and social distancing orders, the following modifications will be made until research operations allow adequate in-person contact.

1. Data collection surveys as described above will be conducted by telephone with the possibility of using Doximity (HIPAA secured videohealth) in some occasions.
2. Subjects will be compensated for data collection visits with a gift card instead of cash. Gift cards will be purchased online from major online retailers and mailed directly to subjects.
3. Subjects will be offered the option to complete the Hemoglobin A1c test and Cholesterol panel at home using FDA-approved home test kits from Home Access Health Corporation. Each test requires a finger stick using a lancet (provided) to produce 5 drops of blood for the sample. The total time required to complete the tests is 20-30 minutes. The following steps will be taken to inform subjects about the kits and obtain results remotely.
  - a. Data collectors will call subjects to provide details about the kits and determine if they are willing and able to complete the lab tests at home.
  - b. If so, coordinator will prepare one of each kit to be mailed to the subject. Coordinator will sanitize work surfaces thoroughly and wear gloves and a mask while packaging any kits.
  - c. Each kit has an identification number which will be linked to the subject's study ID. Home Access also requires a date of birth (DOB) to identify each sample. To protect the subject's PHI, we will create a master list with shifted DOBs for subjects using the REDCap date shifting feature. With this feature, REDCap randomly shifts dates up to 364 days upon downloading the data. The shifted DOB and the study ID will be used to label the kits.
  - d. A list of assigned kits with shifted DOBs and study IDs will be sent to Home Access via a secure FTP (SFTP) server. No PHI will be sent to Home Access.
  - e. The subjects will complete the tests with guidance from the data collector (over the phone or Doximity) and mail them to the lab using the prepaid envelope provided by Home Access.
  - f. Samples will be processed by Home Access and results will be sent daily to coordinator via SFTP server.
  - g. A \$20 gift card for completing the home test kits will be sent to subject once a result is confirmed.

Note that all subjects will have the option to decline home testing and wait until research operations resume and they can complete the blood draw per the usual protocol. Subjects who choose to wait will also be compensated \$20 for completing the blood draw *only* for survey data collection visits completed during the COVID-19 pandemic. Once research operations

resume, subjects will be paid as outlined in section 6.2 *Transition and Retention*.

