### **Temporary modifications to data collection during COVID-19 pandemic**

Due to the COVID-19 pandemic and social distancing orders, all pharmacist and health coach contact with participants will be made remotely and not in-person. This includes phone calls and Doximity video telehealth.

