*Temporary modifications to compensation during the COVID-19 pandemic.* Participants may choose to be paid through their preferred electronic pay app (such as QuickPay/Zelle, Venmo, or Paypal) OR a gift card of their choice from a list of online retailers such as Walmart, Target, Amazon, or Visa. Gift cards will be issued in the amounts as described above for each data collection visit and can be mailed, emailed or texted depending on the vendor.

Due to social distancing orders, participants will have the option to complete their HbA1c and cholesterol profiles using a home test kit. They may also choose to wait and come in to the CRC for a blood draw once research operations resume. Because of the added time and effort required for each of these options, an additional \$20 will be given to subjects for lab tests completed during the COVID-19 pandemic only. This additional incentive will not be offered once in-person interviews and phlebotomy resume.

Other retention strategies include: (1) periodic phone calls/ mailings to verify contact information; and (2) use of alternative contact information. We have developed a comprehensive standardized web-based search protocol that includes five people locators, major social networking sites including those with more minority involvement, and the department of corrections database. Searches are conducted on the target individual as well as alternative contacts.

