### **Primary Outcomes**

Univariate comparisons between the two study groups for outcomes and covariates at baseline will be conducted using chi-square tests for categorical variables, Kruskal-Wallis tests for ordinal variables, and t-tests for continuous variables. Non-normal continuous data will be transformed prior to analysis.

In order to provide comprehensive analysis for  $H_1$ , we will extend the usual analysis of crossover designs by including a longitudinal trend component in the first year. Thus, we can examine the time course (0, 6, and 12 months) as linear or quadratic over the first three

measurements. This will allow us to investigate whether changes are made early, and at what rate they continue through the rest of the time period. This analysis permits the comparison of trends between the two conditions. In addition, we will regard subjects as a random effect and will use Gaussian mixed-model estimation (SPSS MIXED). We can then substitute treatment by period interactions for the carry-over effects, and the model can be reduced in a recommended sequence (first omit carry-over, then omit treatment, finally omit period). SPSS MIXED will also be used to explore patterned covariance structures such as compound symmetry and autoregression along with incorporating time-constant and time-varying covariates, such as health literacy or diabetes distress.

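### Under the COVID rule a month-12 A1c/LDL sample can be drawn after the one-year crossover; used as the month-12 value, it would bias the first-year comparison toward zero

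*Protocol*

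**What the plan says.** **The blood draw.** In the COVID modifications to section 6.1, Data Collection, surveys stay on schedule by remote means: "Data collection surveys as described above will be conducted by telephone". Patients are offered home kits for A1c and cholesterol, but "all subjects will have the option to decline home testing and wait until research operations resume and they can complete the blood draw". The compensation paragraph under Transition and Retention repeats the option: "They may also choose to wait and come in to the CRC for a blood draw once research operations resume". Neither place gives a latest date, a visit window or an exception for month 12. Patients who wait receive $20 for the draw, but only "for survey data collection visits completed during the COVID-19 pandemic".

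**The crossover.** Crossover Transition ties the switch to enrollment: "One year after enrollment, the participants receiving" mDAS have it phased out, and "The participants in the usual care group during year 1 will receive" mDAS for the following year. Transition and Retention also places the usual-care switch at the end of year 1. Neither makes the switch conditional on a month-12 sample.

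**Intervention delivery.** The COVID paragraph in section 6.4 changes the mode of contact and does not pause it: "all pharmacist and health coach contact with participants will be made remotely and not in-person".

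**The analysis.** Section 12.0, Primary Outcomes, says "we can examine the time course (0, 6, and 12 months) as linear or quadratic over the first three" measurements. The Sample Size Justification powers the trial on A1c.

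**The concern.** The first-year contrast is mDAS against usual care only for samples taken before the switch. A sample taken afterwards compares patients whose mDAS has been withdrawn with patients who are now receiving it. Both changes push the A1c and LDL differences the same way, toward no difference. Whether a sample is late also depends on the patient's own choice to wait, so late patients need not resemble the rest.

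Month 12 matters beyond the trend model. Section 12.0 defines complete cases for the per-protocol analysis without requiring months 6 and 18, so the month-12 result is one that a complete case does need. It also feeds the 12-month cost-effectiveness ratio and is the natural starting point for the one-year maintenance question.

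**Working it through.** **Sequence check.** Take a usual-care patient whose month-12 visit falls while in-person research is suspended, and follow the text as written.

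| Step | What the protocol provides | Timing |
|---|---|---|
| Month-12 survey | Telephone (6.1, COVID modifications) | On schedule |
| Month-12 A1c/LDL | Home kit, or wait (6.1; Transition and Retention) | If waiting, no upper limit |
| Crossover | One year after enrollment (Crossover Transition) | Fixed, no hold for the sample |
| mDAS delivery | Phone or video (6.4, COVID paragraph) | Continues |

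No rule in the protocol prevents the second row from happening after the third and fourth. For an mDAS-arm patient the same sequence puts the sample after phase-out.

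**Illustration of size.** The protocol gives neither the share of late draws nor the response by the time of the draw, so both are assumptions:

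- f = share of usual-care month-12 samples drawn after crossover.
- g = share of the mDAS effect those patients have gained by then.
- The mDAS arm is assumed to keep its full gain. Any loss after phase-out would shrink the difference further.

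Difference = 1.0 × (1 − f·g), where 1.0 is the planned A1c difference.

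Inputs from the Sample Size Justification: SD 1.8, correlation 0.30, design effect 1.34, two-sided alpha 0.05, power 80%, drop-out 20%, N = 220.

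Reproducing 220 first: a single post-treatment value needs 51 per arm, and 51 × 1.34 / 0.8 gives 86 per arm, 172 in total. A change score has SD 1.8 × √(2 × 0.7) = 2.13 and needs 72 per arm; 72 × 1.34 / 0.8 gives 121 per arm, 242 in total. Neither is 220. That is a separate matter, but it is why three power bases are shown.

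- Stated 80%: power = Φ(2.802 × difference − 1.960), where 2.802 = 1.960 + 0.842.
- At N = 220, effective n per arm = 220 × 0.8 / 1.34 / 2 = 65.7, and power = Φ(difference × √(65.7/2) / SD − 1.960), with SD 1.8 or 2.13.

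| f | g | Difference | Power, stated 80% | Power, single value | Power, change score |
|---|---|---|---|---|---|
| 0 | – | 1.00 | 0.80 | 0.89 | 0.77 |
| 10% | 50% | 0.95 | 0.76 | 0.86 | 0.72 |
| 25% | 50% | 0.875 | 0.69 | 0.80 | 0.65 |
| 50% | 50% | 0.75 | 0.56 | 0.67 | 0.52 |
| 50% | 100% | 0.50 | 0.29 | 0.36 | 0.27 |

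These treat month 12 as the only outcome value. The planned model also uses month 6, so they only approximate the effect on the full longitudinal test.

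**The case against.** Several points against the concern have force.

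- **Coding of late draws.** A reader might infer that a late sample is formally the month-12 value. The only support is the payment sentence, which says who receives $20 and not which time point a result is assigned to. Primary Outcomes names the planned times and does not say that late results are coded at nominal time. This stands, so the bias is conditional on that use.
- **Crossover during the shutdown.** The remote-contact paragraph says how contact is made, not that new crossovers start on time. The one-year rule is general. That crossovers went ahead is a fair reading, but no text confirms it.
- **Exposure.** The month-12 visit must fall in the shutdown, and the patient must decline the kit, return later, cross over first and have responded by then. No enrollment dates are given. The kit is the first offer and earns the same $20, so waiting is not favoured. Early response may also be limited: the Pharmacy Management Protocol puts the first pharmacist visit after a coach visit and allows up to 90 days from enrollment for it.
- **Analysis plan content.** Windows and assignment of late samples to a treatment phase are often left to the SAP. That is true of the analysis rule. It does not answer the order of collection and crossover, which the protocol fixes: an SAP can reclassify a late sample but cannot recover a pre-crossover sample that was never taken.
- **Label.** A1c is not named as the single primary outcome. Aim 1 lists it with blood pressure, LDL and medication adherence. It is the outcome used for sample size.

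**Conclusion.** The concern holds as a conflict between two stated rules. The draw may be postponed without limit, the crossover is set by the calendar, and nothing links them. A month-12 A1c/LDL sample can therefore fall after the treatments have switched. If it is then used as the month-12 value, the A1c and LDL differences are biased toward zero, because both arms move in the direction that narrows the gap.

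The size is unknown. At f = 10% and g = 50% the loss is small (difference 0.95); at f = 50% and g = 50% it is substantial (0.75). Both quantities are assumed. A reader might take the power figures as an estimate of harm to this trial, but the documents give no late-draw frequency and do not show that any month-12 visit was affected. The conclusion is that the text permits the problem and contains no safeguard against it.

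**What to change.** Reconcile the two statements of the waiting option (6.1, COVID modifications; Transition and Retention) with the two statements of crossover timing (Crossover Transition; Transition and Retention):

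1. State that the month-12 A1c/LDL sample is to be collected before crossover, within a window that is the same in both arms and closes when the year-2 phase starts. Define that start as the scheduled beginning of mDAS delivery or of phase-out. Do not use first coach contact as the cutoff: Transition and Retention has coaches preparing usual-care patients before the switch, so such a cutoff could discard on-time samples.
2. Re-offer the home kit before crossover to anyone without a month-12 sample.
3. Record the date of every draw. The protocol links kit identifiers to study IDs but does not list draw dates.
4. Do not count post-crossover draws as month-12 values. Analyse them under their actual date and treatment phase.

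The cost is protocol wording, a date field and some additional missing month-12 values. Item 4 removes the bias from mixing treatment phases but does not restore lost information. If 25% of values were excluded in both arms, effective n would be 65.7 × 0.75 = 49.3 per arm, and power by the formula above would be 0.79 (single value) or 0.64 (change score), close to the diluted 0.80 and 0.65 at g = 50%. Items 1 and 2, which secure the sample in time, therefore matter most.
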